### Blinding

Given the characteristics of the intervention, we will not attempt to blind patients or clinicians.

### Sample size calculation

Taking data in the scientific literature on the rate of vaginal delivery within 24 h after the administration of the study drugs (70% for oral misoprostol [12], 55% for dinoprostone [12] and 54% of vaginal misoprostol [24]) as a reference, we will need to analyse 333 women (111 per arm) to detect significant differences between the groups with a power of 90% and a confidence level of 95%. Assuming a 10% rate of losses during the follow-up period, we will therefore need to recruit a total of 372 women (124 per arm).

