### Statistical analysis

First, we will describe the general characteristics of the sample. For this, percentages with 95% confidence intervals will be calculated for qualitative data and means and standard deviations for quantitative data.

Second, logistic regression analysis will be used to assess the relationship between the intervention received and the primary outcome (vaginal delivery within the first 24 h after administration of the corresponding drug). Crude and adjusted models will be constructed using variables found to be confounding factors in the univariate analysis.

Logistic regression analysis will also be used to analyse the rates of vaginal deliveries at 12 and 48 h after starting induction and the ripening of the cervix at 12 and 24 h. The rates of maternal adverse events (gastrointestinal adverse effects, uterine tachysystole, uterine rupture, uterine hyperstimulation, morbidity, postpartum haemorrhage, and fever) and of caesarean sections will be compared between the groups with a chi-square test.

Third, multiple linear regression analysis will be performed to explore the relationships between duration of the labour (total, and of active and latent phases), the maximum level of pain reported by the woman, 1- and 5-min APGAR scores, umbilical cord pH, and the intervention (vaginal dinoprostone, and oral or vaginal misoprostol). As well as crude models, adjusted models will be built controlling for intervention group. Complications and adverse events including neonatal asphyxia, morbidity, neonatal intensive care unit admission, and mortality and other complications will be compared between groups with a chi-square test.

Both intention-to-treat and per-protocol analysis will be performed. For the intention-to-treat analysis, we will consider all women included in the study who received at least one dose of any medicine. To handle any missing data on satisfaction, we will use multiple imputation techniques, taking into account age, parity and other potentially relevant variables. We will use the IBM SPSS Statistics for Windows, version 22.0, considering a *p* value of < 0.05 to be significant.

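### The stated 90% power is wrong: at the plan's own rates, 111 women per arm give about 64–70% power per oral-versus-comparator contrast

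*Protocol article*

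**What the plan says.** The Sample size calculation section takes its planning rates for the primary outcome (vaginal delivery within 24 h of drug administration) from the literature: "70% for oral misoprostol [12], 55% for dinoprostone [12] and 54% of vaginal misoprostol [24"]. From these it concludes that "we will need to analyse 333 women (111 per arm) to detect significant differences between the groups with a power of 90" per cent, at a 95% confidence level. It then allows for 10% losses and arrives at 124 recruited per arm, 372 in all.

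That section names no test, no contrast and no sidedness. The Statistical analysis section plans a logistic regression for the primary outcome and takes a p "value of < 0.05 to be significant". It specifies no directional test and no multiplicity adjustment. The Aim is to find which of the three options gives the higher rate.

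**The concern.** All the inputs for a power calculation are printed in one paragraph, so the claim can be checked without any outside source. Differences of 15 and 16 percentage points around rates of 55–70% normally need about 200 women per arm for 90% power at a two-sided 5% level. The plan has 111.

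Power is the design's main quantitative assurance for its primary outcome. If it is overstated, a non-significant contrast will be read as a result that had only a 10% chance of missing the planned effect. The real chance would be about three times that.

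**Working it through.** **Inputs.** From the Sample size calculation: p = 0.70 (oral, O), 0.55 (dinoprostone, D), 0.54 (vaginal misoprostol, V); n = 111 evaluable per arm; 10% loss; 95% confidence level. From Randomisation: 1:1:1. Assumption: two-sided α = 0.05, because no direction is stated. One-sided 5% is also shown.

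**Step 1. What reproduces.** The allowance for losses is right: 111 / 0.9 = 123.3, rounded up to 124; 3 × 124 = 372. The fault is therefore in the step from rates to 111 per arm.

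**Step 2. Power per contrast, normal approximation, unpooled variance.** Power = Φ(d / SE − 1.960), with SE = √{[p₁(1−p₁) + p₂(1−p₂)] / n}.

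- O vs D: variance sum 0.2100 + 0.2475 = 0.4575; SE = √(0.4575/111) = 0.0642; 0.15/0.0642 = 2.336; Φ(0.376) = **64.7%**.
- O vs V: variance sum 0.2100 + 0.2484 = 0.4584; SE = √(0.4584/111) = 0.0643; 0.16/0.0643 = 2.490; Φ(0.530) = **70.2%**.

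With pooled variance under the null hypothesis, the figures are 63.8% and 69.2%.

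**Step 3. Overall test, 2 df.** Mean rate 0.5967; Σ(p − mean)² = 0.01607; mean × (1 − mean) = 0.24066. Noncentrality = 111 × 0.01607 / 0.24066 = 7.41. Power against the 5% critical value of 5.99 is **68.2%**.

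**Step 4. Other readings.** The joint rows come from simulation (400,000 trials, pooled z tests).

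| Reading | 111 per arm | 124 per arm (no losses) |
|---|---|---|
| O vs D, two-sided | 64–65% | 69% |
| O vs V, two-sided | 69–70% | 74–75% |
| Overall 2-df test | 68% | 73% |
| O beats both, two-sided | 51% | 57–58% |
| Any of three pairwise tests, two-sided, unadjusted | 81–82% | 85% |
| O vs D, one-sided 5% | 75–76% | 79–80% |
| O vs V, one-sided 5% | 79–80% | 83–84% |
| O beats at least one, one-sided 5%, unadjusted | 90% (89.7–89.8%) | 92–93% |

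Oral versus both vaginal-route arms combined (111 vs 222) gives 78.5% two-sided and 86.8% one-sided.

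**Step 5. Size needed for 90%, two-sided.** n = [p₁(1−p₁) + p₂(1−p₂)] × (1.960 + 1.282)² / d², with (1.960 + 1.282)² = 10.507.

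- O vs D: 0.4575 × 10.507 / 0.0225 = 213.7, so 214 per arm (217 pooled).
- O vs V: 0.4584 × 10.507 / 0.0256 = 188.1, so 189 per arm (192 pooled).
- Overall test: 189.5, so 190 per arm.

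Conversely, with 111 per arm and 54% in the comparator, 90% power is reached at 74.4% in the other arm (unpooled), a difference of about 20 points.

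**Step 6. Where 111 may come from.** For 70% vs 54%, one-sided 5% and 80% power, with (1.645 + 0.842)² = 6.183: 0.4584 × 6.183 / 0.0256 = 110.7, which rounds up to 111. This is a possible explanation only.

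**The case against.** **Sidedness is not stated, and a one-sided 5% test narrows the gap.** True: per-contrast power becomes 75–80%. That is still 10 to 15 points short, and two-sided is the natural reading for a plan that asks which of three options is best.

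**One reading does come close to 90%.** Counting success as oral misoprostol beating at least one comparator, with two unadjusted one-sided 5% tests, gives 89.7–89.8%. The protocol describes no such rule, and the rule leaves the error rate over the two tests uncontrolled. It also does not match the planned analysis. It cannot be taken as what the paragraph means.

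**The origin of 111 is conjecture.** This stands. One numerical match does not show what was done: the pooled formula gives 113, not 111. Nothing here depends on it.

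**The 51% figure uses a success rule that the plan does not set.** This also stands. The Discussion anticipates oral misoprostol as the most effective option but does not require significance against both comparators. The figure illustrates the point; the case rests on the per-contrast and overall results.

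**Low power for 55% versus 54% is not an arithmetic error.** Correct: the planning assumption is that these arms hardly differ. It is worth one sentence in the protocol because the Aim covers all three options, but it is not part of the miscalculation.

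**The harm is conditional.** Low power does not bias the estimate or raise the type I error. It matters mainly if the result is non-significant, which at these rates is much likelier than stated.

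**An unseen analysis plan may add detail.** It may, but it cannot make 111 per arm yield 90% power at these rates.

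**Conclusion.** The power statement is wrong as written. At the protocol's own rates and a two-sided 5% level, 111 per arm give 64–70% power per oral-versus-comparator contrast and 68% overall, against a claimed 90%. The shortfall is 20 to 26 points per contrast, or 10 to 15 points if one-sided 5% tests were intended. The probability of missing the planned effect is 30–36% per contrast (two-sided), not 10%. Even with no losses, power is 69–75% per contrast.

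The choice of formula (pooled or unpooled) moves these figures by about one point. The only material assumption is sidedness, and neither choice gives 90% for either contrast. The check takes the planning rates as given and says nothing on whether they are realistic.

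**What to change.** Correct the Sample size calculation paragraph so that rates, N, power, test, contrast and sidedness agree. If the sample size is kept, wording along these lines would do:

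> With 111 evaluable women per arm and a two-sided 5% level, power is about 65% for 70% versus 55%, about 70% for 70% versus 54%, and 68% for the overall three-group test. Power of 90% applies to differences of about 20 percentage points. The trial is not powered to separate dinoprostone from vaginal misoprostol at the assumed rates.

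Add that non-significant contrasts will be reported as risk differences with 95% confidence intervals and not as evidence of equal efficacy.

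This costs one paragraph and a less favourable power figure. It needs no more patients and no change to treatment.

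The alternative is to keep 90% and enlarge the trial. For both oral contrasts at 90% each (pooled formula), that means 217 evaluable per arm (651). With 10% losses, 217 / 0.9 = 241.1, so 242 recruited per arm (726), nearly double the planned 372. That is the sponsor's choice; correcting the statement is needed either way.

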### Variables

The data collected will be recorded on case report forms, safeguarding patient confidentiality at all times. The primary outcome will be the rate of vaginal delivery (normal or instrumental) within the first 24 h after drug administration.

The secondary outcomes include cervical status (Bishop score of 6 or over, assessed 12 and 24 h after drug administration), percentage of caesarean sections, use of oxytocin and, if so, the total dose, duration of latent and active phases and the pushing stage of labour, induction failure (no progress into the active phase of labour after administering oxytocin for 12 ± 3 h after membrane rupture), uterine tachysystole, hypertonicity, hyperstimulation, or rupture, adverse events including maternal and/or foetal death, pain (assessed on a visual analogue scale), women’s satisfaction with the induction process (assessed using a dichotomous question, asked 2 days after childbirth or on hospital discharge), maternal morbidity (uterine rupture, severe postpartum haemorrhage or intensive care unit admission) and foetal morbidity (1- and 5-min APGAR scores, umbilical cord pH, and neonatal asphyxia, among other variables).

Due to the extensive information about misoprostol and dinoprostone in the literature, it was considered that a data monitoring committee was not needed. We report to the ethics committees yearly on the progress of the trial. Currently, we have no plans to make any major modifications to the protocol, but we will communicate any such modifications to all people involved.

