### Participants

This single-centre open-label randomised clinical trial will be carried out in Araba University Hospital (Spain), a tertiary hospital that conducts approximately 2600 deliveries per year. The study population consists of pregnant women at 41 weeks of pregnancy or more undergoing induction of labour who meet all the inclusion criteria and none of the exclusion criteria.Inclusion criteria: Women are required to be over 18 years old with a singleton pregnancy, cephalic presentation, intact membranes, a Bishop score of less than 6, and a cardiotocographic trace with a foetal heart rate pattern that is reactive with no decelerations, and provide written informed consent.Exclusion criteria: To be eligible, women must not have an allergy or intolerance to any of the study drugs; a history of caesarean section or uterine surgery, or of stillbirth; high parity (four or more previous births); contraindications for vaginal birth, including placenta or vasa praevia; intrauterine growth restriction; gestational hypertension; suspected chorioamnionitis; or blood clotting disorders, epilepsy, liver or kidney disease, or moderate-to-severe heart disease.

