### Randomisation

Selected women will be randomly assigned in a 1:1:1 ratio to the dinoprostone, oral misoprostol or vaginal misoprostol groups using a computer-generated random number sequence. Researchers will be blinded to this randomisation sequence throughout the study. The randomisation will be performed through an online platform that is available 24-h a day and meets data protection requirements.

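### The cervical ripening models at 12 h and 24 h do not fix the baseline Bishop score as a covariate; fixing it is a small, free gain on a secondary outcome

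*Protocol article*

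**What the plan says.** All places are in the protocol article, under Methods/design.

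- **Participants:** eligibility requires "a Bishop score of less than 6", so a score is known before treatment for every randomised woman.
- **Variables:** ripening is a secondary outcome, "cervical status (Bishop score of 6 or over, assessed 12 and 24 h after drug administration"). The primary is separate: "The primary outcome will be the rate of vaginal delivery (normal or instrumental) within the first 24 h after drug administration".
- **Statistical analysis:** logistic regression is planned for the primary outcome, followed by the covariate rule: "Crude and adjusted models will be constructed using variables found to be confounding factors in the univariate analysis". The next paragraph extends logistic regression to "the ripening of the cervix at 12 and 24 h". It names no covariate and does not say whether the screening rule carries over.
- **Randomisation:** women are "randomly assigned in a 1:1:1 ratio". **Blinding:** "we will not attempt to blind patients or clinicians".
- **Sample size calculation:** 111 analysed women per arm, set for the primary outcome. No power is stated for ripening.

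**The concern.** The baseline Bishop score is the same measurement as the outcome, taken earlier. A woman who enters at 5 reaches the ripe state with one more point; a woman who enters at 1 needs five. It is therefore likely to be one of the strongest predictors of a score of 6 or over at 12 h or 24 h.

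The article leaves its use open in two ways. The ripening models may be crude. Or they may inherit a screening rule that picks confounders from the data. In a randomised trial a strong predictor tends to be balanced across arms, so a screen that looks for confounding can drop it, although it is the variable most worth adjusting for. The screening criterion is not stated either, so the adjusted ripening result would depend on a choice made after the data are seen.

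What is at stake is some power, and a fixed model, for the only listed outcome that measures the cervix directly.

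**Working it through.** **Inputs from the documents.** Entry score below 6; ripe at 6 or over; 111 per arm; two-sided 5% level. The plan gives no figure for ripening, so there is none to reproduce.

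**Inputs assumed.** The documents give neither the spread of Bishop scores nor the reading error. True entry score ~ N(μ, 1.5) within 0–13; a reading is the rounded true score plus N(0, e) error; women are kept if the entry reading is below 6; true change ~ N(gain, s). Centre: μ = 3.5, e = 1.0.

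**Models compared**, two arms of 111, Wald test of β:
- crude: logit P(ripe) = α + β·arm
- adjusted: logit P(ripe) = α + β·arm + γ·(entry score)

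**Step 1: how prognostic is the entry score?** Centre case, gain 2.0, s = 2, by entry reading:

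| Entry reading | 0 | 1 | 2 | 3 | 4 | 5 |
|---|---|---|---|---|---|---|
| Points needed to reach 6 | 6 | 5 | 4 | 3 | 2 | 1 |
| Share of women | 5.4% | 10.0% | 18.1% | 24.3% | 24.3% | 18.0% |
| Ripe | 14.9% | 24.0% | 33.5% | 44.4% | 55.4% | 66.6% |

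**Step 2: power**, 10,000 simulated trials per row:

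| μ | e | Gains | s | Ripe rates | Crude | Adjusted | Difference (points) |
|---|---|---|---|---|---|---|---|
| 3.5 | 1.0 | 2.0 v 2.7 | 2 | 45.5% v 56.2% | 36.5% | 38.4% | 1.9 |
| 3.5 | 1.0 | 2.0 v 2.7 | 1.5 | 44.8% v 57.2% | 45.8% | 51.2% | 5.3 |
| 3.5 | 1.0 | 2.5 v 3.3 | 2 | 53.1% v 65.1% | 43.6% | 47.5% | 3.9 |
| 3.5 | 1.0 | 1.5 v 2.2 | 2 | 38.0% v 48.5% | 35.5% | 38.5% | 3.0 |
| 3.5 | 0.5 | 2.0 v 2.7 | 2 | 45.7% v 57.2% | 40.4% | 46.0% | 5.6 |
| 3.5 | 1.25 | 2.0 v 2.7 | 2 | 45.4% v 55.7% | 34.4% | 35.9% | 1.5 |
| 2.5 | 1.0 | 2.0 v 2.7 | 2 | 33.6% v 44.0% | 34.9% | 38.5% | 3.5 |
| 4.5 | 1.0 | 2.0 v 2.7 | 2 | 56.5% v 66.9% | 35.1% | 38.0% | 2.9 |

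Differences are taken before rounding; their simulation error is about 0.3 to 0.4 points. With equal gains (2.0 v 2.0) the rejection rates are 5.0% crude and 5.1% adjusted, so adjustment does not disturb the type I error.

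**Step 3: why power rises.** In a logistic model adjustment does not shrink the standard error of β. It moves the estimate further from zero than it widens the error. First row: crude 0.433/0.271 = 1.60, adjusted 0.481/0.287 = 1.68. Then Φ(1.60 − 1.96) = 36% and Φ(1.68 − 1.96) = 39%, which agrees with the table.

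**Step 4: is the cut at 6 itself distorting?** First-row arms, taking a true score of 5.5 or more as truly ripe: measured 45.4% and 56.2%, true 45.1% and 56.7%. False positives (6.4%, 5.9%) and false negatives (6.1%, 6.5%) nearly cancel. The arm difference is 10.8 points measured against 11.6 true.

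**The case against.** **Covariate lists for secondary outcomes are often left to an analysis plan, which is not shown.** This stands in part. The documents do not exclude baseline adjustment, so one cannot say that it will be absent. But the article does fix a covariate rule, and that rule is data-driven screening. The supportable statement is that adjustment for baseline is not prespecified.

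**The gain is small and the outcome is secondary.** Both are true, and they limit the weight of the point.

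**A reader might infer more: that success begins exactly where eligibility ends, so a one-point re-reading by an unblinded examiner makes a responder.** The documents do not support this.

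- Below 6 at entry and 6 or over later are the two halves of one unfavourable/favourable split, and the outcome is labelled as a status, not a gain.
- The one-point route exists only for women entered at exactly 5, and their share is not given.
- Responder rates computed for women with no true change do not describe three arms that all receive an active prostaglandin; with real change the misreadings nearly cancel (step 4).
- Bias between arms needs misreading that differs by arm. Open-label care permits that, but nothing shows it, and it is an inference that the Bishop examiner is one of the unblinded clinicians. Misreading equal in all arms would only dilute a difference.

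**Stronger remedies are also tempting.** Requiring a gain of at least 3 points as well would remove about 10% of women from the ripe group in the simulated arms (9.8% and 9.5%), and 78% to 82% of those removed are truly ripe. Analysing the full score gave higher power (57–73%, against 37–46% for the crude binary cut), but only with a score for all 111 women per arm. The sample size section expects 54% to 70% to deliver vaginally within 24 h, and a delivered woman has no natural Bishop value.

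**Conclusion.** The point holds as a free improvement. The entry Bishop score is known for every woman and determines her distance from the cut-off, yet the plan does not fix it in the ripening models. Fixing it is worth about 2 to 6 percentage points of power (1.5 to 5.6 over the scenarios run).

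That range rests on assumed Bishop variability, on one pairwise comparison, and on a score for every woman. It suits the 12 h reading better than the 24 h reading, where the value depends on how delivered women are counted. Power stays well below 80% in every scenario, so adjustment does not make ripening a well-powered comparison.

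The primary outcome is not affected. The ripening cut-off is not an error, and biased scoring is not shown.

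**What to change.** In Statistical analysis, add to the sentence on ripening: the 12 h and 24 h models include treatment group and the pre-treatment Bishop score (as a linear term) as fixed covariates, whatever the univariate screening shows. State that this adjusted model is the main ripening analysis and that the crude one is supportive. Because the adjusted odds ratio is conditional on baseline and will usually lie further from 1 than the crude one, report the plain ripening percentages per arm beside it.

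Keep a Bishop score of 6 or over as the definition. A minimum-gain rule or an analysis of the full score may be added as labelled supportive analyses, but neither should replace it.

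Cost: one or two sentences. The score is already needed for eligibility, so there is no new data collection and no change to the sample size or the primary analysis.

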### Statistical analysis

First, we will describe the general characteristics of the sample. For this, percentages with 95% confidence intervals will be calculated for qualitative data and means and standard deviations for quantitative data.

Second, logistic regression analysis will be used to assess the relationship between the intervention received and the primary outcome (vaginal delivery within the first 24 h after administration of the corresponding drug). Crude and adjusted models will be constructed using variables found to be confounding factors in the univariate analysis.

Logistic regression analysis will also be used to analyse the rates of vaginal deliveries at 12 and 48 h after starting induction and the ripening of the cervix at 12 and 24 h. The rates of maternal adverse events (gastrointestinal adverse effects, uterine tachysystole, uterine rupture, uterine hyperstimulation, morbidity, postpartum haemorrhage, and fever) and of caesarean sections will be compared between the groups with a chi-square test.

Third, multiple linear regression analysis will be performed to explore the relationships between duration of the labour (total, and of active and latent phases), the maximum level of pain reported by the woman, 1- and 5-min APGAR scores, umbilical cord pH, and the intervention (vaginal dinoprostone, and oral or vaginal misoprostol). As well as crude models, adjusted models will be built controlling for intervention group. Complications and adverse events including neonatal asphyxia, morbidity, neonatal intensive care unit admission, and mortality and other complications will be compared between groups with a chi-square test.

Both intention-to-treat and per-protocol analysis will be performed. For the intention-to-treat analysis, we will consider all women included in the study who received at least one dose of any medicine. To handle any missing data on satisfaction, we will use multiple imputation techniques, taking into account age, parity and other potentially relevant variables. We will use the IBM SPSS Statistics for Windows, version 22.0, considering a *p* value of < 0.05 to be significant.

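### The primary model's covariates are chosen by univariate screening of the trial data with no ranking of crude against adjusted, and the linear models adjust only for the exposure itself; the impact is modest and the repair is cheap

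*Protocol article*

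**What the plan says.** All the analysis wording is in the protocol article, Statistical analysis section.

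- **Primary outcome.** The plan is that "logistic regression analysis will be used to assess the relationship between the intervention received and the primary outcome", and then: "Crude and adjusted models will be constructed using variables found to be confounding factors in the univariate analysis". No candidate list or selection criterion is given, nothing restricts candidates to baseline variables, and nothing says whether the crude or the adjusted result answers the primary question.
- **Linear models.** Labour durations, maximum pain, APGAR scores and cord pH are to be related to treatment; the list of terms ends "umbilical cord pH, and the intervention (vaginal dinoprostone, and oral or vaginal misoprostol". The next sentence reads: "As well as crude models, adjusted models will be built controlling for intervention group". No other covariate is named for these models.
- **Allocation** (Randomisation section). "Selected women will be randomly assigned in a 1:1:1 ratio". No stratification factor is mentioned.
- **Baseline data available to all** (Participants section). Eligibility requires "a Bishop score of less than 6" and excludes women with four or more previous births, so baseline Bishop score and parity (0 to 3) are known for every woman. The Statistical analysis section uses parity only as a predictor when imputing missing satisfaction data.

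**The concern.** Confounding in the observational sense does not arise at baseline in a randomised comparison: differences between arms are chance. A screen that looks for confounders in the trial data reacts to that chance, and the covariate set is known only after outcomes have been seen. Three things are at stake.

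1. **Meaning of the primary estimate.** The odds ratio is non-collapsible: adding a prognostic covariate changes its value even with no confounding. If the data choose the covariates, they also choose which odds ratio is reported.
2. **Two unranked primary results.** A crude and an adjusted result with no order between them leave room to favour the more convenient one.
3. **Open candidate list.** Without a baseline-only limit, a variable affected by treatment is not ruled out.

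For the linear models, the adjusted analysis as written adds nothing to the crude one.

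**Working it through.** **Inputs from the article.** 111 women analysed per arm; 70% (oral misoprostol) against 55% (dinoprostone); p < 0.05. **Assumed, not in the article.** 35% parous; parity odds ratio 4 or 6; Bishop score odds ratio 1.65 or 2.0 per SD; 9 candidate covariates.

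**1. Anchor: crude power at the plan's sample size.** With p̄ = 0.625, √(2p̄q̄) = √0.46875 = 0.6847 and √(p₁q₁ + p₂q₂) = √0.4575 = 0.6764:

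z = (0.15·√111 − 1.96·0.6847)/0.6764 = (1.580 − 1.342)/0.6764 = 0.353, so power ≈ 64%.

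The article's 90% at 111 per arm is not reproduced: the same two-sided formula needs 217 per arm. That is a separate matter and this point does not depend on it. The 64% serves only to check the simulated crude power below.

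**2. Power of the possible models (simulation, 70% vs 55%, 111 per arm).**

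| Model | Power over the two sets of assumed effects |
|---|---|
| Crude | about 64–65% |
| Fixed: parity + Bishop score | 70% and 74% |
| Screened on association with outcome | 69% and 74% |
| Screened on association with both arm and outcome | 64–67% |

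Repeat runs put crude power at 63–65% and fixed adjustment at 70–74%. With 1,500 replicates the Monte Carlo standard error is about √(0.65·0.35/1500) = 1.2 points, so that spread is expected. In one repeat, outcome screening picked parity in 98–100% of trials and Bishop score in 88–98%, which is why it nearly matches fixed adjustment. Screening that also requires an arm imbalance usually drops them.

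**3. Type I error (simulation under the null).**

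- *Three arms of 111; 5 or 10 standard normal baseline covariates, log-odds 0.4 each; 4,000 replicates; standard error about 0.3 points.* Screened on outcome at p < 0.05, the adjusted model alone rejects 4.9–5.4%, and a fixed set containing all covariates 4.9–5.4%. Taking whichever of crude or screened is significant rejects 7.0–7.4%.
- *Same setting, screened on both arm and outcome at p < 0.20.* Adjusted alone 3.5–4.1% (conservative); whichever is significant 5.4–5.9%.
- *Covariates with no prognostic value.* Whichever is significant stays at 4.6–5.4%.
- *Nine candidates.* Crude 5.0%, screened 4.7%, whichever is significant 6.7–6.8%.

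**4. Linear models.** Let the crude design matrix be X = [1, D₁, D₂], with D₁ and D₂ the arm indicators. Controlling for intervention group appends D₁ and D₂ again: 5 columns, rank still 3. In a numerical example the two arm contrasts were 0.3126 and −0.0156 in both fits. The adjusted model is the crude model.

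**The case against.** The strongest reply has five parts.

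- **The plan does adjust.** It would be wrong to infer that strong baseline predictors go unused and that the whole 6–9 points between crude and fixed adjustment are lost. If screening is on outcome, almost all of that gain is kept. This stands. The loss against the planned adjusted model appears only if confounding is read as association with both arm and outcome, which the article leaves open.
- **False positives are not inflated by the plan as such.** A reader might infer that they are. Each model on its own holds about 5% or less, and the article nowhere says that the significant one will be reported. This stands: the 6–7% depends on that conduct, which an unranked pair permits but does not prescribe.
- **Post-randomisation covariates are not proposed.** A reader might infer that oxytocin use or phase durations will be adjusted for. The article lists them as secondary outcomes, and a confounder properly excludes consequences of treatment. This stands as to intent. The gap matters because oxytocin use depends on arm by design: after tachysystole with later loss of activity, Table 1 sends the dinoprostone arm to oxytocin while the misoprostol arms restart treatment. A purely empirical screen could therefore pick it up.
- **A condensed article leaves covariate lists to the analysis plan.** True of an unnamed list, and that absence is not the point. The article states a selection rule and a linear adjustment; a fixed list elsewhere would contradict the first.
- **The linear sentence may be a drafting slip on secondary, exploratory models.** Probably so, and the crude comparison there remains valid. It still cannot be carried out as a distinct analysis.

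**Conclusion.** The point holds as a modest one that should be corrected before analysis. The article fixes a data-driven covariate rule for the primary model, leaves crude and adjusted unranked, and specifies a linear adjustment that is empty.

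Under the assumed covariate effects, fixed adjustment gains 1 point of power or less over screening on outcome, and about 6–8 points over screening on both arm and outcome. Type I error rises to about 6–7% only if the better of the two results is the one reported. With weaker prognostic effects these figures shrink. The direction of the linear-model finding needs no assumption, because it follows from the wording.

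The documents do not support saying that the primary comparison is biased, that treatment-affected covariates are planned, or that this point explains the sample-size discrepancy.

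**What to change.** In the Statistical analysis section:

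1. Delete the univariate screening.
2. Fix parity (0 vs 1–3) and baseline Bishop score in advance as covariates in the logistic models, alongside treatment arm.
3. Name one model as primary and report the other as supportive.
4. State that only baseline variables may enter as covariates.
5. In the linear models, replace the adjustment for intervention group with the same two baseline covariates.

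**Cost.** Wording only: eligibility screening already establishes both covariates, so no extra data or participants are needed. The one real trade-off is that the adjusted odds ratio is conditional. It will differ from the marginal one, which at the planning rates is (0.70/0.30)/(0.55/0.45) = 1.91. Because the trial's aim concerns rates, report the crude rates by arm beside it. Standardised risk differences are an optional addition and need an extra estimation step.
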